**Patient factors**								
Patient/parent health literacy	Confidence in filling out medical forms, with options from extremely confident (0) to not at all confident (4); scores ≥ 2 considered low health literacy [71–73]			X				
Visit type	Annual/wellness exam, acute visit, or chronic condition follow-up						X	X
Patient demographics	*-Insurance:* None/public insurance, private insurance *-Race/ethnicity:* American Indian or Alaska Native, Asian, Black, Hispanic, Native Hawaiian or Pacific Islander, multiracial/other, White, prefer to self-describe *-Sex*: Male, female, or self-describe *-Age*: Continuous variable			X				X
Respondent demographics (patient or parent)	*-English proficiency*: Very well, well, not well, not at all *-Education*: < high school, high school graduate, > high school *-Respondent relationship to patient*: Self, mother, father, other guardian			X				
**Provider and clinic barriers, organized by Theoretical Domain Framework and COM-B categories** [37]								

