#### Aim 1: Compare the effectiveness of two implementation strategies, alone and in combination, to improve use of interpretation and comprehension for patients/parents with language barriers seen in adult/pediatric primary care settings

We hypothesize that, compared to educational modules, provider access to mobile video interpreting will lead to (*H1*) greater odds of interpreter use for visits with patients/parents with language barriers (primary outcome) and (*H2*) better comprehension among patients/parents with language barriers. We also hypothesize (*H3*) that mobile video interpreting and educational modules together will yield greater odds of interpreter use than either strategy alone.

To test *H1* and *H3*, we will use assigned strategy and data collected during phases 1 and 2. Under the SMART design, comparisons of first-stage interventions, comparisons of second-stage interventions, and comparisons of the adaptive intervention with both stages can be conducted simultaneously using standard software with a technique called a “weighted and replicated” regression approach, using weighted generalized estimating equations (GEE) [66, 97]. Weighted GEE allows us to work with binary outcomes and weights and adjust for clustering within providers. Within-clinic correlations will be assessed by including clinic-specific random effects in our regression models and estimating the intra-cluster correlation coefficients. Significance of the intra-cluster correlation coefficients will be examined by comparing models with and without clinic-specific random effects using likelihood ratio tests. If no strong within-clinic correlation is detected, we will use fixed-effects regression models for their better power; otherwise, estimates and inference based on random-effects regression models will be reported. *H1* and *H3* will be tested using the Wald test and robust standard error estimates [66, 97]. Model-based estimates of odds ratio comparing education to mobile video interpreting or both will be reported, along with 95% confidence intervals [98].

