To test *H2*, our analytic sample will include only patients who completed a post-visit survey (*n* = 648). A weighted GEE logistic regression model predicting patient/parent comprehension at the visit level will be estimated. Baseline covariates will include the clinic, patient demographics (age, sex, language), and patient comorbid conditions [99–102], pooled at the provider level. Model-based estimates of the odds ratio comparing education to mobile video interpreting or both will be reported, along with 95% confidence intervals computed via parametric bootstrapping [98].

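### The comprehension (H2) model is fitted per surveyed patient but enters patient covariates as provider aggregates, which gives up some precision for no stated reason

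*Protocol article*

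**What the plan says.** In the H2 paragraph of Data analysis, Aim 1, the unit of analysis is the surveyed visit: "A weighted GEE logistic regression model predicting patient/parent comprehension at the visit level will be estimated". The adjustment set follows: "Baseline covariates will include the clinic, patient demographics (age, sex, language), and patient comorbid conditions", and then the qualifier "pooled at the provider level". No reason is given for pooling. The grammar leaves open whether the qualifier applies to every patient covariate or to comorbid conditions only.

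For inference on H2, the article states odds ratios with "95% confidence intervals computed via parametric bootstrapping". The preceding paragraph, on interpreter use, says that H1 and H3 "will be tested using the Wald test and robust standard error estimates"; no such statement is made for H2. That paragraph also gives the reason for the method: "Weighted GEE allows us to work with binary outcomes and weights and adjust for clustering within providers".

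**The concern.** The outcome varies between patients of the same provider, and so do age, sex, language and comorbidity. A provider mean takes one value for all of that provider's patients, so it cannot explain why one understood the diagnosis and another did not. That explanatory power is the main gain from covariate adjustment in a model fitted per patient.

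Pooling also moves these covariates to the level at which strategy was randomised, where independent units are scarce. Patient-level covariates draw mostly on several hundred surveys, while pooled ones draw on a few dozen providers. At stake is precision for the trial's secondary, effectiveness outcome.

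**Working it through.** **Inputs from the article.** 55 providers randomised; up to 9 lost, leaving 46 (Interpreter use). 648 surveys, 216 per group, for a 14-point difference with at least 80% power (Patient/parent comprehension). Four survey languages (Patients). 3 to 5 organizations (Study design and randomization). Surveys per provider: 648/46 = 14.1, or 648/55 = 11.8.

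**Assumed, because the article does not give them.** Two-sided alpha 0.05, base proportion, provider intra-cluster correlation (ICC), covariate effects, four clinics, and a single comorbidity term.

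**1. The plan's own figure.** A two-proportion test with 216 per group, p versus p + 0.14 and no clustering gives power between 83.1% (p near 0.43) and 99.2% (p = 0.80) over p = 0.30 to 0.80. The stated 80% reproduces.

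**2. Provider-level parameters, q.**
- Patient-level covariates: intercept 1 + arm 1 + clinic 3 = 5.
- All covariates pooled: 5 + age 1 + sex 1 + language 3 + comorbidity 1 = 11.
- With four comorbidity terms: 14.

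**3. What this costs in the test.** A simple small-sample test multiplies the robust standard error by √(K/(K − q)) and uses t with K − q degrees of freedom. With K = 46:
- q = 5: √(46/41) × 2.020 = 1.059 × 2.020 = 2.14.
- q = 11: √(46/35) × 2.030 = 1.146 × 2.030 = 2.33.

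The estimate must therefore exceed 2.33 rather than 2.14 uncorrected standard errors.

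**4. Simulated power.** 3000 runs, 46 providers × 14 surveys, ICC 0.05 on the latent scale, true log odds ratio 0.6. That effect takes 0.50 to about 0.65, since e^0.6 = 1.822 and 1.822/2.822 = 0.646.

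| Adjustment | Mean estimate / empirical SD | Power, corrected test |
|---|---|---|
| Clinic only | 0.539/0.214 = 2.52 | 0.703 |
| Clinic + all patient covariates pooled | 0.553/0.219 = 2.53 | 0.698 |
| Clinic + comorbidity alone pooled | 0.571/0.214 = 2.67 | 0.752 |
| Clinic + patient-level values | 0.588/0.218 = 2.70 | 0.763 |

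Pooling everything costs 0.763 − 0.698 = 0.065 and leaves power about where clinic adjustment alone puts it. Pooling comorbidity alone costs 0.763 − 0.752 = 0.011. Other runs, with ICC 0.05 and 0.10 and covariate log-odds effects of 0.2 to 0.5, gave 52–67% pooled against 61–73% patient-level, so 6 to 9 points at the ends of the ranges. A further set gave 0.67 against 0.74.

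**5. Simulated type I error, 46 providers, nominal 0.05.**
- Uncorrected robust Wald: 0.090–0.106 with all covariates pooled, 0.069–0.082 with comorbidity alone pooled, 0.070–0.075 patient-level.
- With the correction in step 3: 0.046–0.063 across all simulated scenarios, pooled or patient-level.
- Variance from a bootstrap drawing independent binary outcomes, across all simulated scenarios: 0.056–0.103 pooled, 0.067–0.111 patient-level.

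**6. Simulated bias, no true effect.** Case mix of the surveyed patients was shifted between arms by 0.3 and 0.6 SD. The mean log odds ratio was 0.24 and 0.47 unadjusted, 0.01 and 0.00 pooled, and 0.01 and 0.00 patient-level. The empirical SD was 0.22 pooled against 0.21 patient-level at the smaller shift, and 0.28 against 0.22 at the larger.

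**The case against.** Three stronger readings are tempting, and the article does not support them.

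**Pooling inflates the error rate.** A reader might carry the Wald test with robust standard errors over from H1 and H3. The article does not state it for H2. The excess in step 5 disappears with a degrees-of-freedom correction, and pooling adds none under the independent-outcome bootstrap. Part of the excess remains with patient-level values (about 0.07), so it comes from having few providers.

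**Pooling leaves bias from who was surveyed.** Strategy is assigned by provider, so a case-mix difference between first-stage arms is a difference in provider means, and means of the surveyed patients can adjust for it (step 6). This assumes the means are taken over surveyed patients and not over the provider's whole panel. The contrast with the combined strategy is less clear. A provider may contribute single-strategy surveys in phase 1 and combined-strategy surveys in phase 2, and one mean over both phases could not follow a change in case mix. Simulated shifts of 0.3 and 0.5 SD gave a bias of about 0.09 and 0.15 in the log odds ratio. But that requires pooling across phases and no phase term, and the article states neither.

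**Pooling explains power as low as 52–67%.** Patient-level values reached only 61–73% in the same runs. Most of the gap to 80% is clustering: at ICC 0.05 the design effect is 1 + (14 − 1) × 0.05 = 1.65. That is a separate matter.

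The best defence is that the phrase may cover comorbidity alone. The loss is then trivial, and there may be a practical reason for it: comorbidity is absent from Table 1, and the only record abstraction described under Patient/parent comprehension is the documented diagnosis. That stands, and it limits both the size of the point and how firmly per-patient comorbidity can be asked for. It does not justify pooling age, sex and language. Table 1 lists age and sex from the patient survey and administrative data, and the survey population is defined by language.

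**Conclusion.** The mismatch between a visit-level outcome and provider-level patient covariates is in the text, but its consequence is modest. On the broad reading it costs about 6 to 9 points of power under a valid small-sample test, with little or no gain over clinic adjustment alone. On the narrow reading it costs about 1 to 2 points. The first-stage comparison is not biased by it. Added type I error, about 0.09–0.11 against 0.07, would arise only if an uncorrected robust Wald test were used for H2.

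These sizes rest on the assumed ICC, covariate effects, between-provider spread and clinic count. Replication of responders and response-dependent weights were not simulated. Because the outcome is secondary and the remedy nearly free, this is a cheap improvement of minor severity.

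**What to change.** In the H2 paragraph of Data analysis, Aim 1, delete the words "pooled at the provider level". State instead that the model includes clinic as a fixed effect and each surveyed patient's own age, sex and language. Enter comorbidity per patient where existing records supply it; if they do not, keep it as the only provider-level term and say so.

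Adding health literacy, which Table 1 already collects through the item "Confidence in filling out medical forms", is optional. In simulation it moved power from 61–73% to 61–75%, and leaving it out is not an error.

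The cost is a change of wording, slightly more data linkage, and imputation of a few missing covariate values. Per-patient comorbidity could require extra abstraction, which is why the fallback is offered.

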#### Aim 2 Explore mobile video interpreting and education implementation strategies’ ability to activate putative provider-level mechanisms

We predict that implementation via mobile video interpreting will activate mechanisms that are more directly and strongly linked to provider behavior, while education’s mechanism activation will more often affect intrapersonal barriers without changing behavior.

We will use a quantitative plus qualitative approach to explore putative mechanisms, where both are analyzed together to understand data in context [88]. Interviews will be audio-recorded, transcribed, translated as appropriate, and reviewed for accuracy. Using an iteratively developed codebook, we will code all data stratified by interpreter use and TDF attributes, upload data into Dedoose Version 9.0.17 for thematic analysis [103–105], and use the 6 analysis steps outlined by Braun and Clarke [106]. Data synthesis will be conducted from code reports utilizing an annotation and tabular system. We will analyze provider and patient data separately.

Video-recording analysis will be based on our previously developed coding scheme [36], with modifications based on coding the first 5 videos. We expect coding to include communication/interpretation method, duration, interpretation technical difficulties (e.g., dropped calls), interpreter or device positioning in room, provider use of jargon and acronyms, and clarifications between provider and interpreter. Initial videos will be double coded, until kappa statistics for interrater reliability are greater than 0.75. Subsequent videos will be single coded, with a random 10% double coded. Fidelity to assigned strategy will be defined as use of mobile video interpreting for assigned providers and use of best practices for communicating through an interpreter for education-assigned providers.

Qualitative analysis of interviews and video recordings will occur with reference to provider quantitative data, for example, by interpreter use (high vs low) and survey-reported TDF attributes, following NIH guidelines for mixed-methods best practices [107]. Provider interviews and videos will be considered as a set, to assess for changes over time, by assigned strategy. The relationships we investigate will be guided by preliminary causal pathway models (Figs. 2 & 3). These models, developed with best available evidence, lay out the putative mechanisms of each implementation strategy, including organizational and intrapersonal moderators, specific barriers, and proximal and distal outcomes. In this approach, we will explore hypothesized relationships and invite emergent mechanisms we had not previously considered given this work’s exploratory nature. Little is known about the mechanisms by which particular strategies influence interpreter use or even if things like acquiring facts serve as mediators on the pathway from strategy to outcome [108, 109]. Per Kazdin, identifying mediators and mechanisms of change allows greater reason and parsimony in selecting implementation strategies and should allow attainment of greater improvements over time as we understand exactly how improvement occurs [110]. We will refine our causal pathway diagrams and generate new ones reflecting the evidence gathered through this study.

#### Aim 3: Determine the incremental cost-effectiveness from a healthcare organization perspective of each implementation strategy (mobile video interpreting, education, and both)

We hypothesize that, relative to educational modules, mobile video interpreting will be more cost-effective (*H4a*) per additional interpreted clinic visit and (*H4b*) per additional instance of patient comprehension.

The estimated incremental cost-effectiveness ratios (ICER) will provide evidence of the resources required to increase interpreted clinic visits and improve patient comprehension [111]. Our goal is to support decision-making about which strategy healthcare organization leaders may choose to implement, and thus, we will estimate ICERs from the organization perspective.

Effectiveness measures will be based on Aim 1 analyses; cost data will come from two sources. The first source is administrative, including vendor invoices and budgets for payroll. Costs that cannot be determined will be estimated with a micro-costing approach in which unit cost multipliers are applied to the quantity of each type of service or resource utilized; examples include the use of shared resources (space, office equipment) and opportunity costs experienced by clinic staff. All cost data are summed to obtain total costs [112], using an approach we have used previously [113, 114]. While mobile video interpreting-assigned providers may also have used other professional interpretation, we will assign mobile video interpreting-related costs to the mobile video interpreting and combination groups and nonmobile video interpreting interpreter costs (which would not be necessary if a clinic used mobile video interpreting only) to the education group. Interpreter costs will be based on actual usage from vendor invoices, attributed to assigned group. Education module development will be annuitized over the study period. Time costs for providers (time on modules, learning to use mobile video interpreting) and study staff (reminder emails, mobile video interpreting support) will be estimated using the mean hourly wage from the National Compensation Survey, plus fringe rates from the Bureau of Labor Statistics Employer Costs for Employee Compensation. Provider costs due to own-device use for mobile video interpreting will be estimated with hardware depreciation allowances per the US Internal Revenue Code. Costs will be inflation-adjusted to common-year dollars using the Personal Health Care Expenditure Deflator or Personal Consumption Expenditure price index [112].

We will calculate total costs associated with each implementation strategy by summing the above costs. To test *H4a*, we will calculate the ICER for each additional interpreted clinic visit, by calculating the difference in total costs for (i) mobile video interpreting vs education and (ii) mobile video interpreting plus education vs education, and then divide by the difference in number of professionally interpreted visits for providers assigned to (i) mobile video interpreting vs education and (ii) mobile video interpreting plus education vs education. To test *H4b*, we will calculate the ICER for each additional instance of patient comprehension. To do so, we will calculate the difference in total costs for (i) mobile video interpreting vs education and (ii) mobile video interpreting plus education vs education and then divide by the difference in proportion of patients who correctly reported their diagnosis for providers assigned to (i) mobile video interpreting vs education and (ii) mobile video interpreting plus education vs education.

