**Methods:**

We will conduct a type 3 hybrid implementation-effectiveness study in 3–5 primary care organizations, using a sequential multiple assignment randomized trial (SMART) design. Our primary implementation outcome is interpreter use, calculated by matching clinic visits to interpreter invoices. Our secondary effectiveness outcome is patient comprehension, determined by comparing patient-reported to provider-documented visit diagnosis. Enrolled providers (*n* = 55) will be randomized to mobile video interpreting or educational modules, plus standard interpreter access. After 9 months, providers with high interpreter use will continue as assigned; those with lower use will be randomized to continue as before or add the alternative strategy. After another 9 months, both strategies will be available to enrolled providers for 9 more months. Providers will complete 2 surveys (beginning and end) and 3 in-depth interviews (beginning, middle, and end) to understand barriers to interpreter use, based on the Theoretical Domains Framework. Patients who use a language other than English will be surveyed (*n* = 648) and interviewed (*n* = 75) following visits with enrolled providers to understand their experiences with communication. Visits will be video recorded (*n* = 100) to assess fidelity to assigned strategies. We will explore strategy mechanism activation to refine causal pathway models using a quantitative plus qualitative approach. We will also determine the incremental cost-effectiveness of each implementation strategy from a healthcare organization perspective, using administrative and provider survey data.

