#### Interpreter use

Interpreter vendor invoices will be collected from companies that clinics currently contract with; mobile video interpreting invoices will be managed by the study team. All professional interpreter invoices (not just mobile video interpreting) will be matched to clinic visits for patients who use a language other than English (all languages) for enrolled providers. We will calculate baseline interpreter use for enrolled providers for the six months pre-randomization and then randomize 1:1 to education or mobile video interpreting, stratified by baseline use and clinic. We will calculate interpreter use, both overall and strategy consistent, continuously throughout phases 1–3; other data collection will end after phase 2.

For analysis, interpreter use will be defined as a dichotomous variable at the level of the clinic visit. Visits with patients who use a language other than English with any billed professional interpreter use will be coded as “yes,” and the remainder will be coded as “no.”

Sample size calculations consider aim 1 group comparisons (mobile video interpreting, education, combination) at the end of phase 2. We assume loss of up to 9 providers (e.g., to job change; 16%) over the study; we expect attrition (up to 27%) in provider interviews and surveys, but that will not impact aim 1 power. With 5796 total encounters with patients who use a language other than English (7 visits/provider/month), we expect 1932 non-English visits per group, which will provide > 80% power to detect a 5% difference in proportion of professionally interpreted visits by groups [46, 57]. This will be readily feasible with administrative data.

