### Data analysis

Primary quantitative analyses will be conducted using an intention-to-treat approach. Provider and patient characteristics will be summarized overall and by strategy. Missing data will be minimized through communication with participants regarding the importance of completing surveys and interviews, participant incentives, offering multiple languages and modalities for survey and interview completion, and completing surveys and interviews on-site when possible. For our primary outcome, we expect interpreter invoice data to be complete, given our previous experience [12, 46, 57]. We will track interpreter use for all enrolled providers for the entire study, even if they do not complete interviews or surveys. For our secondary outcome, diagnosis comprehension, patterns of data missingness will be examined. We expect randomization will help protect against imbalance in unobserved confounders, so our main concern will be with missing data. We will conduct sensitivity analyses based on multiple imputations to assess the impact of missing data, in which we will generate multiple imputed datasets with missing values imputed by pooling information from observed data, and then combine statistical inferences across the multiply-imputed datasets [94–96].

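### Aim 3 leaves the other-mode interpreter costs of mobile video providers out of their group's costs but keeps the resulting visits and comprehension in its effects

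*Protocol article*

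**What the plan says.** **Cost rule.** The Aim 3 section of the protocol article first concedes the overlap: "While mobile video interpreting-assigned providers may also have used other professional interpretation". It then states that "we will assign mobile video interpreting-related costs to the mobile video interpreting and combination groups and nonmobile video interpreting interpreter costs" are split by type, with "nonmobile video interpreting interpreter costs (which would not be necessary if a clinic used mobile video interpreting only) to the education group". The sentence after that reads "Interpreter costs will be based on actual usage from vendor invoices, attributed to assigned group".

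**Effect rule.** The same section takes effectiveness from the Aim 1 analyses. For H4a the cost difference is to be taken and then "divide by the difference in number of professionally interpreted visits for providers assigned to (i) mobile video interpreting vs education", and likewise for the combination versus education. For H4b the divisor is the difference in the proportion of patients who report their diagnosis correctly, again by the provider's assigned group. The section on interpreter use defines an interpreted visit from all modes: "All professional interpreter invoices (not just mobile video interpreting) will be matched to clinic visits".

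**Access.** The Methods paragraph of the abstract says that providers are "randomized to mobile video interpreting or educational modules, plus standard interpreter access". Neither group is confined to its assigned strategy.

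**The concern.** The two halves of the ratio follow different rules. A telephone or in-person interpreted visit by an MVI-assigned provider adds one visit to the MVI group's effect, but its invoice is not in that group's cost. The same happens in the combination group. H4b is affected through the same cost difference, because comprehension is counted by assignment and not by interpreter mode.

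The reason given is that a clinic using MVI alone would not need the other services. The trial does not observe such a clinic. Table 2 lists lower spending on in-person interpreting among the outcomes that MVI is meant to affect, yet the rule sets other-mode spending in the MVI groups to zero instead of measuring it.

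H4a and H4b hypothesise that MVI is the more cost-effective strategy, and Aim 3 is meant to help organization leaders choose. An error that can only favour the hypothesised winner matters there, all the more because it is divided by a small difference in effect.

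**Working it through.** **The plan's own figure.** The article gives no unit costs, no non-MVI share and no ICER, so there is no cost result to reproduce. The visit count used for scale does reproduce: (55 − 9) providers × 7 visits × 18 months = 5796, and 5796 / 3 = 1932 per group.

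**Notation.** Em and Ee are interpreted visits in the MVI and education groups. s is the share of Em interpreted without MVI. cm and co are the unit costs of MVI and of other interpretation.

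- Full accounting: ΔC = Em[(1 − s)cm + s·co] − Ee·co
- As written: ΔC = Em(1 − s)cm − Ee·co
- Amount omitted from the MVI group: s·co·Em
- Shift in the H4a ICER: −s·co·Em / (Em − Ee)

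The omitted amount cannot be negative, and it vanishes only at s = 0.

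**Inputs for the illustration.** From the article: 1932 visits per group and a 5-point difference. Assumed: 55% versus 50% use, and interpreter costs only, with other strategy costs set equal.

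- Em = 0.55 × 1932 = 1062.6
- Ee = 0.50 × 1932 = 966
- Em − Ee = 96.6
- Em / (Em − Ee) = 11, so the shift is −11·s·co per extra visit

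**Equal unit cost c.**

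- Full: (1062.6c − 966c) / 96.6 = +c at every s
- As written, s = 0.25: (796.95c − 966c) / 96.6 = −1.75c
- As written, s = 0.5: (531.3c − 966c) / 96.6 = −4.5c
- Sign change: s = 1 − 966 / 1062.6 = 0.091, about 9%

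**Unequal unit costs**, with cm = $50 assumed. Each cell gives the full-cost ICER, then the as-written ICER, in dollars per extra interpreted visit.

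| co | s = 0.25 | s = 0.5 | s = 0.75 |
|---|---|---|---|
| $30 | +195 / +112.5 | +140 / −25 | +85 / −162.5 |
| $50 | +50 / −87.5 | +50 / −225 | +50 / −362.5 |
| $80 | −167.5 / −387.5 | −85 / −525 | −2.5 / −662.5 |

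First cell in full: MVI cost 1062.6 × (0.75 × 50 + 0.25 × 30) = 47,817; education cost 966 × 30 = 28,980; difference 18,837; divided by 96.6 gives 195. The as-written value is 195 − 11 × 0.25 × 30 = 112.5.

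**H4b.** The omitted cost in the numerator is the same s·co·Em. The divisor is the difference in comprehension proportions.

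**The case against.** The strongest defence is the sentence "Interpreter costs will be based on actual usage from vendor invoices, attributed to assigned group", which on its face is ordinary costing by assigned group. On that view the split rule could concern only avoidable contracts and dedicated hardware, and most of the problem would go. The wording does not fit this. The rule speaks of interpreter costs, and it opens with MVI-assigned providers using other professional interpretation. If every invoice already followed assignment, the rule and its MVI-only justification would do nothing. The later sentence therefore contradicts the rule and does not cure it. At the least, the two must be reconciled.

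It is also fair to say that the rule is disclosed and describes a scenario that leaders might care about. That stands, but a scenario needs cost and effect on the same footing.

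A reader might infer more than the article supports:

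- **That MVI will be made to look cost-saving whatever the data.** Only the direction of the error is certain. With co = $30 and s = 0.25 the as-written ICER stays positive. With co = $80 it is negative under both rules. The article itself notes that video costs more than telephone, so equal unit costs are a simplification. Module development, staff and provider time, and device costs also enter the totals and are left out of the illustration.
- **That the omitted costs are also added to education.** The wording allows it, and the shift would then double (−4.5c instead of −1.75c at s = 0.25 with equal unit costs). The text does not settle this.
- **That the rule breaches "Primary quantitative analyses will be conducted using an intention-to-treat approach".** That sentence governs the primary quantitative analyses and does not clearly reach the Aim 3 costing.

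**Conclusion.** The concern holds. As written, the Aim 3 rule and the H4a and H4b effect measures do not match, and the rule conflicts with the sentence that follows it. Where MVI-assigned providers use any other interpretation, the MVI group's cost is understated by s·co·Em, always in MVI's favour; the combination group is affected in the same way.

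At the article's planning scale, and with use of 55% versus 50% assumed, each 10 percentage points of non-MVI use lowers the H4a ICER by 1.1 × co (11 × 0.10). With equal unit costs and interpreter costs alone, that turns the sign once s passes about 9%. The use rates, the share and the unit costs are assumptions, so neither the real size nor a real reversal can be stated from the article. The Aim 1 analyses of interpreter use and comprehension are unaffected.

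**What to change.** Delete the split-attribution rule. In the primary ICERs for H4a and H4b, charge each assigned group all professional interpreter invoices, in every mode, for its eligible visits, plus the costs of its strategy. Keep the sentence on actual usage by assigned group as the single rule, and say that it covers every mode.

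If the MVI-only clinic is of interest, keep it as a labelled scenario with both sides consistent, for example by re-costing the group's other-mode visits at the MVI rate. It should not drop those costs while keeping their effects. Nor should it count only MVI-interpreted visits as the effect: that selects on provider behaviour after randomization, and it does not suit the comprehension outcome in H4b.

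The cost is a change of wording in Aim 3. The invoices for all modes are already to be collected and matched to enrolled providers' visits, so no new data are needed.
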